### Inclusion and exclusion criteria

Inclusion:Aged 18 years or over.A documented diagnosis of schizophrenia or delusional/psychotic illness (*International Classification of Diseases, version 10* (ICD-10) F20.X and F22.X or *Diagnostic and Statistical Manual of Mental Disorders* (DSM)-equivalent) or bipolar disorder (ICD-10 F31.X or DSM-equivalent).Current smoker, smoking at least five tobacco cigarettes per day.Express a desire to cut down or quit smoking.

Exclusion:Pregnant or breast-feeding women.Known comorbid drug or alcohol dependency (as recorded in GP or psychiatric records).Currently receiving advice from a stop smoking advisor.Non-English speaking.Lack of capacity to consent.

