### Sample size

The SCIMITAR+ trial has been powered to detect a relative increase in quitting of 1.7 (baseline quit rate 20%, intervention quit rate 34%) using a two-sided significance level of 5% at 80% power. This would require a sample size of 314 participants using equal (1:1) randomisation. Allowing for a 20% loss to follow-up would give a total sample size of at least 393. We therefore propose to recruit 400 participants in total to ensure sufficient power.

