The number of cigarettes smoked per day will be compared between the two groups using a Poisson regression model, adjusting for the same covariates as the primary analysis. If the variance of the data is larger than the mean, this may give an indication that the data are over-dispersed. In this case, a negative binomial model will be run. If the data are zero-inflated, then a zero-inflated Poisson or negative binomial model will be used. Incidence rate ratios and their associated 95% confidence intervals and *p* values will be provided.

The FTND, the Motivation to Quit questionnaire (MTQ), the Patient Health Questionnaire-9 (PHQ-9), the Generalised Anxiety Questionnaire-7 (GAD-7), the 12-item Short Form Health Survey (SF-12) physical component, SF-12 mental component scores, and BMI will all be analysed in the same way. Scores at 6 and 12 months will be compared between treatment groups using a repeated-measures covariance pattern mixed model including as fixed effects: baseline score, treatment group, time and a treatment group × time interaction term. Different covariance structures for the repeated measurements, that are available as part of STATA v13 (or later), will be explored and the most appropriate pattern will be used for the final model. Diagnostics including Akaike’s information criterion will be compared for each model (smaller values are preferred). Model assumptions will be checked. Estimates of the difference between treatment groups will be derived at all time points with 95% confidence intervals and *p* values.

Self-reported number of attempts to quit, periods of cessation, electronic cigarette use, and adverse events will be summarised descriptively by treatment group.

A complier average causal effect (CACE) analysis for the primary outcome will be conducted to obtain unbiased estimates of the intervention effectiveness in the presence of full compliance. We will define compliance with the intervention for those allocated to bespoke smoking cessation service (BSC) as the number of sessions attended.

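### If the zero-inflated branch is taken, the cigarettes-per-day rate ratio no longer describes all participants but in effect compares continuing smokers

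*Protocol article*

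**What the plan says.** In the Data analysis section of the protocol article, "The number of cigarettes smoked per day will be compared between the two groups using a Poisson regression model". The covariates are those of the primary analysis: baseline number of cigarettes and treatment group, with centre as a random effect. A negative binomial model replaces Poisson if the data are over-dispersed. Then comes a second switch: "If the data are zero-inflated, then a zero-inflated Poisson or negative binomial model will be used". Whichever model results, the output named is the same: "Incidence rate ratios and their associated 95% confidence intervals", with p values.

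Three other statements bear on this:

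- The Data analysis section opens by putting all analyses on an intention-to-treat basis, covering every randomised patient with data in the allocated group.
- The inclusion criteria require: "Current smoker, smoking at least five tobacco cigarettes per day".
- The Sample size section plans on "baseline quit rate 20%, intervention quit rate 34" per cent.

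The article does not say whether treatment enters the inflation part of the model, whether an estimate from that part will be reported, or whether an overall mean will be derived from the two parts.

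**The concern.** A zero-inflated model splits the outcome in two. The inflation part models the probability of being a structural zero. The count part models the number of cigarettes among the rest, and the incidence rate ratio comes from that part. Everyone enters this trial smoking at least five a day, so zeros at follow-up come mainly from quitting. The model is fitted to all participants with data, but the ratio it reports is in effect a comparison of those still smoking. Treatment is expected to change who is in that group, so the comparison is not protected by randomisation.

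One label, incidence rate ratio, therefore covers two quantities, and the distribution of the data decides which is published. A fall in consumption achieved by quitting could appear in the results as a ratio near 1 and be read as no effect on consumption.

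**Working it through.** **1. The plan's own figures.** Inputs from the Sample size section: 20% and 34%, two-sided 5%, 80% power, 1:1. With pooled variance and no continuity correction:

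n per arm = [1.96 × √(2 × 0.27 × 0.73) + 0.8416 × √(0.20 × 0.80 + 0.34 × 0.66)]² / 0.14² = 156.7, rounded up to 157, or 314 in total.

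314 / 0.80 = 392.5, rounded up to 393. Both stated figures reproduce. The article gives no figure for the cigarettes-per-day analysis.

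**2. Would the switch occur?** The mean among continuing smokers is not given; assume 10 to 20 a day. Zeros expected from a count distribution alone:

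- Poisson, exp(−m): 0.0045% at m = 10, and less above that.
- Negative binomial with assumed dispersion 0.3, (1 + 0.3m)^(−1/0.3): 0.98% at 10, 0.34% at 15, 0.15% at 20.
- Negative binomial with assumed dispersion 0.6 and m = 10: 7^(−1/0.6) = 3.9%.

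The plan expects 20% to 34% quitters. The switch is very likely. It is not certain, because the article states no criterion for zero-inflation and an ordinary negative binomial can absorb some zeros by raising its dispersion.

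**3. The two quantities.** Let m be the control-arm mean among continuing smokers and r the intervention-to-control ratio of those means.

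- Overall ratio of means = (1 − 0.34) × r × m / [(1 − 0.20) × m] = 0.825 × r
- Count-part ratio ≈ r
- Odds ratio for being a zero = (0.34/0.66) / (0.20/0.80) = 2.06

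| r (assumed) | Count-part ratio | Overall ratio |
|---|---|---|
| 0.90 | 0.90 | 0.743 |
| 1.00 | 1.00 | 0.825 |
| 1.10 | 1.10 | 0.908 |

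At r = 1 the whole 17.5% reduction is absent from the count-part ratio. For r between 1 and 1/0.825 = 1.21, the two ratios lie on opposite sides of 1.

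**4. Simulation at r = 1.** There were 157 per arm and 100 runs per scenario, with no baseline or centre adjustment. Means and dispersions are assumed. Entries are the median ratio and the percentage of runs with p < 0.05.

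| Mean, dispersion | Zero-inflated, treatment in both parts | Zero-inflated, constant inflation | Poisson, robust errors | Negative binomial, model-based errors |
|---|---|---|---|---|
| 15, 0 | 1.004, 3% | 1.004, 3% | 0.829, 66% | 0.829, 24% |
| 15, 0.3 | 1.002, 1% | 1.000, 1% | 0.814, 50% | 0.814, 22% |
| 10, 0.3 | 0.998, 3% | 0.993, 3% | 0.828, 42% | 0.828, 16% |
| 20, 0.3 | 1.004, 3% | 1.003, 3% | 0.849, 37% | 0.849, 12% |
| 10, 0.6 | 1.010, 3% | 0.981, 4% | 0.823, 27% | 0.823, 18% |

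With 100 runs, the Monte Carlo standard error of a rejection rate is at most √(0.5 × 0.5/100) = 5 percentage points. The median inflation-part odds ratio was 1.92 to 2.19, against 2.06 in theory. The zero-inflated ratio is near 1 whether or not treatment enters the inflation part. Poisson and negative binomial give the same estimates here, but model-based negative binomial errors cost much of the power.

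**The case against.** **The quitting effect is measured elsewhere.** A reader might infer that the trial loses the effect it was designed to find. It does not. CO-verified cessation at 12 months is the primary outcome, and the same model is repeated for CO-verified cessation at 6 months and self-reported cessation at 6 and 12 months. That makes four analyses of cessation beside which this ratio would be read. This stands, and it limits the harm to one secondary outcome.

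**Cutting down is also an aim.** The trial admits people who want only to reduce, and the sessions cover reduction as a route to stopping. Consumption among continuing smokers is a fair question. It follows that a ratio near 1 is not a general prediction: if the intervention also reduces smoking among continuers, the count-part ratio falls below 1. This stands too. But the article presents the analysis as a comparison of the two groups, not of continuing smokers.

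**Baseline cigarettes are adjusted for.** One might infer that if lighter smokers quit preferentially, the ratio would be pushed above 1. The stated adjustment blunts that mechanism. It does not remove selection on unmeasured characteristics.

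**The analysis plan may report both parts.** The article does not say that inflation-part results will be withheld, and such detail may sit in a separate analysis plan not available here. That silence is therefore not the criticism. The criticism is of what is stated: a data-driven switch, and one named effect measure whose meaning the switch changes.

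**Conclusion.** The point holds for this secondary outcome. The contrast of 0.825 with about 1.00 rests only on the planned quit rates and on equal consumption among continuing smokers; with unequal consumption the two ratios still differ by the factor 0.825. The likelihood of the switch, and the rejection rates of 27% to 66% for robust Poisson and 1% to 4% for the zero-inflated ratio, rest on assumed means and dispersions and an unadjusted simulation. They are illustrations, not the power of this trial.

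The count-part ratio sits poorly with the intention-to-treat basis set for all analyses, because it is not a contrast of the groups as randomised even though everyone with data enters the fit. A reader might go further and conclude that the main result is at risk or that zero-inflated models must be abandoned. The document supports neither: the primary outcome, its test and the sample size are untouched, and a zero-inflated model is usable if the overall ratio is derived from it.

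**What to change.** State the treatment effect first: the ratio of mean cigarettes per day over all participants with data, with quitters entered as 0. Estimate it by Poisson regression with robust standard errors and the stated covariates, whatever the degree of over-dispersion or number of zeros. Negative binomial is acceptable only with robust errors, for the loss of power shown above.

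If a zero-inflated model is kept, derive the marginal mean ratio from both parts as the treatment effect and report the inflation-part effect beside it. Label the count-part ratio as conditional on continued smoking and not a randomised comparison.

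The cost is a sentence or two in the plan and some extra analysis work; no new data are needed. The downside is that reduction among continuing smokers becomes a labelled supplementary result.

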### Interventions

#### Smoking-cessation intervention

This is a complex intervention involving a bespoke smoking-cessation service provided by a mental health professional trained in smoking-cessation interventions. The mental health smoking-cessation practitioner (MH-SCP) will work in conjunction with the participant and the participant’s general practitioner (GP) or mental health specialist to provide a smoking-cessation service individually tailored to the participant’s needs. The participant will be offered between eight and 12 sessions with the MH-SCP. The intervention will be delivered according to the National Centre for Smoking Cessation and Training’s guidelines with the following specific adaptations for people with SMI: in line with National Institute of Health and Care Excellence (NICE) guidelines for smoking cessation [17]:The possibility of providing several sessions prior to setting a ‘quit date’.Recognising the purpose of smoking in the context of their mental illness, such as the use of smoking to relieve side effects from antipsychotic medication (and how this will be managed during a cessation attempt).The need to involve other members of the multidisciplinary team in planning a successful quit attempt for those with complex care needs and multiagency programmes of care.A greater need for home visits, rather than planned visits in GP surgeries (for some clients with mental illness, the home environment is the optimum place to work).Providing additional face-to-face support following an unsuccessful quit attempt or relapse.Informing the GP and psychiatrist of a successful quit attempt so that they can review antipsychotic medication doses if the participant’s metabolism changes.

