### Control group

This will be a ‘usual care’ control group whereby the participants will be signposted towards usual care for their area. Usual care varies according to where the participant is geographically located and is dependent on local commissioning arrangements. One example consists of participants attending their local GP service on a fortnightly basis to have their expired carbon monoxide (CO) measured by the in-house smoking-cessation practitioner and to collect their ongoing nicotine replacement therapy (NRT) prescription. In other areas participants are referred to a local smoke-free NHS service for the same fortnightly meetings but with an additional initial assessment of nicotine dependence and motivation to quit as well as requiring participants to set a ‘quit day’ when they will stop smoking. In some instances, smoke-free services offer weekly individual or group meetings for motivational and behavioural support at a local centre or pharmacy. In another example participants may visit their GP who provides an NRT prescription and refers patients to a local council-funded project for individual behavioural support.

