### Outcome measures

Data will be collected from participants at baseline and at 6 and 12 months post randomisation. Baseline and follow-up assessments will take place during face-to-face meetings with the participant in order to measure height and weight to calculate the Body Mass Index (BMI), and to take CO readings. As face-to-face follow-up is preferred every effort will be made to collect, as a minimum, a reduced set of data by this method. Where it is not possible to meet with the participant for face-to-face follow-up data collection, the participant will be offered the option of completing the questionnaires by telephone or have the questionnaires sent to them by post for them to complete and return. If it is not possible to make contact with the participant for follow-up, a family member or friend named by the participant at their baseline interview as a person who could be contacted, will be asked to verify the participant’s smoking status.

The primary outcome measure will be cessation of smoking at 12 months assessed according to the Russell standard. Smoking cessation will be defined as having an expired-air CO measurement of less than 10 ppm *and* self-reporting as a quitter (responding ‘not even a puff’ to the question ‘Have you smoked in the last week?’).

Secondary outcomes at 6 and 12 months post randomisation will include measures of smoking status, general mental health functioning, BMI, health-related quality of life, health service use, and adherence with smoking-cessation advice from MH-SCP (Table 1). The flow of participants through the trial is shown in Fig. 2.

**Table 1 Tab1:** Outcome measure and collection time point

Assessment	Time point (months post randomisation)		
	Baseline	6	12
Eligibility and consent			
Eligibility	X		
Consent	X		
Background and follow-up			
Personal details, general health	X		
Body Mass Index	X	X	X
Mental health details			
Mental health history	X		
Current mental health status	X	X	X
Current medications	X	X	X
Referrals to mental health services		X	X
Admissions to hospital related to mental health		X	X
Smoking details			
Smoking history	X		
Current smoking status	X	X	X
Use of electronic cigarettes	X	X	X
Use of smoking-cessation services	X	X	X
CO measurement	X	X	X
Adverse event reporting	Ongoing collection		
Questionnaires			
Fagerström Test for Nicotine Dependence (FTND) [17]	X	X	X
Motivation to Quit questionnaire (MTQ)	X	X	X
Patient Health Questionnaire (PHQ-9)	X	X	X

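### Adverse events are collected continuously and tabulated by arm whatever route they surfaced by, while only one arm is offered 8 to 12 extra trial-delivered sessions; the safety table can overstate events in that arm

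*Protocol article*

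**What the plan says.** In the protocol article, Table 1 (Outcome measures) ties every other post-randomisation item to the 6- and 12-month assessments. Adverse event reporting is the one row marked "Ongoing collection". The Data analysis section then states: "electronic cigarette use, and adverse events will be summarised descriptively by treatment group". It plans no test or confidence interval for these events, and no breakdown by how an event was found.

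The schedule of contact differs by arm. For the intervention: "The participant will be offered between eight and 12 sessions with the MH-SCP". For controls: "participants will be signposted towards usual care for their area", with the qualification that "Usual care varies according to where the participant is geographically located and is dependent on local commissioning arrangements". The assessments shared by both arms are set out under Outcome measures: "Data will be collected from participants at baseline and at 6 and 12 months post randomisation". The Randomisation and blinding section says that neither therapists nor participants can be masked.

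**The concern.** A by-arm count of events is interpretable when an event has about the same chance of being recorded in either arm. Here collection is open-ended in time, and between the shared assessments the only contacts that the trial itself delivers are in one arm. If an event raised at an MH-SCP session is recorded at the time, while a similar event in a control participant has to come through the 6- or 12-month assessment or a clinician, the two columns of the table rest on different levels of ascertainment.

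The Background section describes common beliefs that smoking relieves anxiety and helps with depression. An excess of events under a cessation intervention that came only from closer contact could feed those beliefs. In the other direction, a genuine excess could be waved away as a reporting effect. With no record of source, the trial could not distinguish the two.

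**Working it through.** The plan gives no adverse event rate, capture rate or expected count, so there is no figure of its own to reproduce on this point. The check has two parts.

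**1. Scheduled contacts after randomisation with researchers or the MH-SCP**

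- Control: 2 (6 and 12 months; Outcome measures).
- Intervention: 2 + 8 = 10 to 2 + 12 = 14 (Outcome measures and Smoking-cessation intervention). This is a maximum, since it assumes that every offered session is attended. The Data analysis section itself treats the number attended as the measure of compliance.

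**2. What unequal ascertainment does when there is no true difference**

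Inputs:

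- 200 participants per arm: 400 recruited, 1:1 (Sample size; Randomisation and blinding).
- True risk of an event p = 20% in both arms. *Assumption.*
- r0 = probability that an event is captured through channels common to both arms. *Assumption*, 0.5 to 0.9.
- s = probability that the sessions capture an event the common channels would miss. *Assumption*, 0.25 to 0.75.

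Formulas:

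- Recorded in control = 200 × p × r0
- Recorded in intervention = 200 × p × [1 − (1 − r0)(1 − s)]
- Apparent risk ratio = [1 − (1 − r0)(1 − s)] / r0, in which p cancels

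For example, with r0 = 0.7 and s = 0.75, capture in the intervention arm is 1 − 0.3 × 0.25 = 0.925. The counts are 200 × 0.20 × 0.925 = 37 against 200 × 0.20 × 0.7 = 28, a ratio of 1.32.

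| r0 | Control recorded | Intervention recorded (s = 0.25 to 0.75) | Apparent ratio |
|---|---|---|---|
| 0.5 | 20 | 25 to 35 | 1.25 to 1.75 |
| 0.7 | 28 | 31 to 37 | 1.11 to 1.32 |
| 0.9 | 36 | 37 to 39 | 1.03 to 1.08 |

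A slightly more extreme pair, capture of 0.50 against 0.90 (r0 = 0.5, s = 0.8), gives 0.90/0.50 = 1.80. With s = 0, which is what restricting the table to common channels achieves, the ratio is 1.00 for every r0.

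So, with equal true risk, the direction is fixed once s is above zero, but the size depends almost wholly on r0. If the common channels already find nine events in ten, the distortion is negligible.

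**The case against.** The strongest reply is that the causal link is not in the document. The article does not say who elicits adverse events, whether the MH-SCP reports them, or from which sources they come. The entry in Table 1 describes timing, not a reporting route. A journal article leaves such procedures to the full protocol, which may set a symmetric one. This stands, and it is why the point is conditional. A reader might infer that events told to the MH-SCP reach the trial and that those told to a control participant's GP do not; the text supports neither statement. Clinicians in both arms have a route to the trial: the GP and mental health specialist receive a letter after randomisation, and the Withdrawal section lets them, as well as the practitioner, withdraw a participant. Some usual care involves weekly or fortnightly meetings. These shared channels raise r0 and shrink the effect. They do not remove it unless they capture everything.

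A reader might also infer a falsely significant result. With a true risk of 30% and capture of 60% against 90%, 18% and 27% would be recorded, and z = 0.09/0.0415 = 2.17. No such test is planned, and other equally arbitrary inputs give little: a true 20% with capture of 70% against 85% gives 14% and 17%, with z about 0.8. The z values should not be relied on.

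Nor can it be said that the trial will be uninformative about mental-health harm. PHQ-9, GAD-7 and the SF-12 mental component are measured at 6 and 12 months in both arms and modelled with confidence intervals. Mental-health admissions and referrals are taken at the same assessments and summarised by arm.

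Finally, dropping session-reported events from every by-arm display could hide real harm from the intervention. That objection is right, and the fix below avoids it.

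**Conclusion.** The point holds in a limited form. Ongoing collection, unequal trial-delivered contact and a by-arm summary that ignores the route of ascertainment are all stated in the article. Together they allow the adverse event table to overstate events in the intervention arm, provided that events mentioned at MH-SCP sessions are recorded. The apparent ratio with no true difference is about 1.03 to 1.8 under assumed capture rates. None of those rates comes from the documents, so the true size is unknown and may be trivial. The consequence is a safety table that could be misread, not an invalid test, and the symmetric mental-health measures limit what depends on it. The change is worth making because it is cheap and because the source of an event is hard to reconstruct later.

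**What to change.** - Keep ongoing collection, and keep the full by-arm listing of all events.
- Record the source of each event: 6- or 12-month assessment, MH-SCP session, clinician or records. Allow more than one source, so that an event raised at a session and again at an assessment still counts as found through a common channel.
- Ask the same adverse event question at 6 and 12 months in both arms, however the assessment is carried out.
- Add a by-arm table limited to events ascertained through channels common to both arms, and name it as the basis for between-arm interpretation.
- Show events that surfaced only at MH-SCP sessions as a separate, labelled line, without withholding them.

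The cost is one form field, one question and one extra table, and less if the full protocol's forms already hold some of this. The common-channel table will omit some events, and recall at 6 and 12 months is imperfect, but the full listing still shows every recorded event. If follow-up is already under way, the source field and the split table can still be introduced for events from then on.
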